**Figure 1 F1:**
[figure not shown]
**Flowchart**.

We have not conducted preliminary studies on this subject. Yet there is sufficient literature available proving the effectiveness of this intervention, as mentioned before. There is however some experience with the use of pulsed electromagnetic fields in the treatment of scaphoid fractures in the medical centers in Arnhem, Nijmegen and Hoorn. Considering the hospital in Hoorn, with an adherence of 175.000 patients, pulsed electromagnetic fields-treatment of 13 patients within a period of 9 months has taken place. In Nijmegen, where the participating hospital has an adherence of 275.000 patients, 37 patients with a scaphoid fracture were initially treated with PEMF within a period of 2 years. So concerning the quantitative feasibility of this study, if we extrapolate these numbers to the total region of 4 hospitals with an adherence of around 1.5 million patients, we suspect that inclusion of 100 patients within a period of 1 year should be possible.

Concerning the practical feasibility of the study, the device will be attached to the plaster with additional soft cast after the transducer coil has been applied on the skin above the fracture site. The patient cannot move or displace the device. Pilot studies using the PEMF device for the same indication have confirmed that most patients do not experience any inconvenience because of the device. No adverse effects of PEMF have been recorded. So no limitations are expected concerning the feasibility of the intervention.

The research question for the economic evaluation is:

Is the use of PEMF for fresh scaphoid fractures potentially cost-effective when compared with care as usual from a societal point of view?

The economic evaluation will include both a cost-effectiveness analysis and a cost-utility analysis from a societal perspective. For the cost-effectiveness analysis, the incremental cost-effectiveness ratio (ICER) will be calculated and expressed as the incremental costs per consolidation (see power-analysis). This means that the difference in total treatment costs between the intervention group and care as usual will be divided by their difference in effectiveness (i.e. consolidation). In addition, for the cost-utility analysis, the incremental costs per Quality Adjusted Life Years will be calculated. For this purpose, the health states of the SF36, a questionnaire developed to measure health related quality of life, will be converted to utilities.

### Regarding cost-analysis

Resource use of the following cost-categories will be measured:

Within health care: control visits, X-ray, CT-scan, emergency visits, costs of the intervention (i.e. device). Outside health care: productivity loss, travel costs. The total number of workdays lost will be measured by using modules of the PRODISQ, Productivity and Disease Questionnaire at baseline, 12, 24 and 52 weeks[40]. The costs of productivity loss will be calculated by means of the friction cost method, based on the average standardized wages per hour. The friction cost method takes into account the time, which is needed to replace a sick employee in order to restore the production at the original level [15]. Similar to the clinical study, the time horizon for the economic evaluation will be from the moment of inclusion until 12 months follow-up. Within the context of this study, no costs occur after one year, therefore discounting will not be applied. Total treatment costs will be calculated by multiplying volumes of use with the costs per unit. Unit costs will be derived from the hospital financial department or the Dutch guidelines for cost-calculation [15] Indirect costs (in this case general hospital overhead) will be allocated to the direct costs as an overall percentage, in accordance with the Dutch guidelines for cost calculation.

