Current treatment strategies are unable to deal with this problem. The number of complications following conventional treatment, being immobilization in a cast is, as mentioned before, quite high and surgery is generally performed only if complications in healing occur. Results of operative treatment are variable [11] and furthermore operative treatment for complicated healing of scaphoid fractures (e.g. delayed or non-union) is often initiated in a late phase, most often months after the fracture occurred, which again can have severe socio-economical consequences[10].

The exact incidence of scaphoid fractures in the Netherlands is difficult to estimate. On the one hand, literature indicates that approximately 24.000 carpal fractures (of which 21.000 scaphoid fractures) are being suspected[1-3]. On the other hand, the estimated incidence of true scaphoid fractures is 35 per year in a hospital with an adherence of 250.000 people. Furthermore, literature suggests that true incidence among suspected fractures of the scaphoid is around 15 to 20%[4,12,13]. On a national level, this would indicate that the total number of diagnosed scaphoid fractures amounts to approximately 3.000. Previous studies showed that even uncomplicated healing leads to a mean employment interruption of 155 days or 22 weeks[10]. The hypothesis is that the use of PEMF can shorten this duration by 30 percent[14]. If we assume that 25% of all scaphoid fractures could be treated with PEMF, then this would lead to an increase in total treatment costs of 750 (25% of 3.000) * €1.250 (costs of PEMF) = €937.500.

Still, from a societal perspective, the use of PEMF could potentially lead to a decrease in workdays lost of 750 (25% of 3.000)* 46 days (30% of 155 days) = 34.500 days. If we calculate the costs of these workdays lost by using the friction cost method, then this reduction could potentially lead to cost-savings of 34.500 * €303.21(cost per day of work lost based on the average of the productivity costs per hour as reported in Oostenbrink et al [15] assuming a work day of 8 hours) * 0.8 (correction factor) = €8.368.596

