Consequences of accelerated consolidation on time off work and social well-being will also be investigated.

2. To determine whether the use of PEMF in acute scaphoid fractures will decrease the incidence of non-unions and avascular necrosis of the scaphoid and therefore the number of secondary surgical interventions. The association of mal-union and non-union of the scaphoid fracture with clinical outcome will also be investigated.

3. To investigate the effect of PEMF in acute scaphoid fractures on functional outcome

4. To investigate the potential cost-effectiveness of PEMF from a societal perspective when compared with care as usual.

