Since standard X-rays are unreliable in determining the degree of consolidation, additional CT-scans will be performed in the follow up after 6 weeks, 12 weeks, 24 weeks and 52 weeks. Quantification of fracture healing with the CT scan is based on formation of callus along the fracture and trabecular ridging[36]. The CT scan at 6 weeks will be important for determining the portion of fractures rapidly healed and determining outcome for the primary endpoint. The CT scan at 12 weeks is important for establishing the portion of patients with a scaphoid fracture showing signs of delayed (and eventually non-) union. The CT-scan at 52 weeks is particularly important for 2 reasons. First of all identification of delayed unions (longer than 4 months) can be confirmed. Secondly, if consolidation was established before, it can be checked at later follow up dates if that conclusion wasn't premature and the fractures are in fact healed. Former studies have pointed out that follow up may reveal non-unions whereas the fracture was considered to be consolidated before [37]. When the fracture has both clinically and radiologically consolidated the plaster will be removed. If the fracture has not consolidated; a new plaster will be made. The timing of the removal of the plaster can vary between six or twelve weeks. Only patients who need immobilization of the fracture (not consolidated fractures) will have a PEMF device on them, for in clinically and radiographically consolidated patients there is no need for further treatment. All patients will receive the same follow up, as described above. If the fracture is not consolidated after twelve weeks, at physical or radiographic examination, yet the patient has no pain, the treatment is finished. If the patient has got pain, he will get a removable splint.

In addition to the physical and radiographic examination, patients will be required to fill in a questionnaire: a SF health survey 36. The SF36 questionnaire appears to be a valid and reliable instrument to measure pain and psychosocial well-being[38]. This will be done after inclusion in the trial, before applying the PEMF device, at 6,9,12,24 and at 52 weeks. For assessment of functional deficit, disability and pain level, the Patient Rated Wrist Evaluation (PRWE) will be used. The PRWE is an easy 15-item questionnaire designed to measure wrist pain and disability in activities of daily living. The PRWE allows patients to rate their levels of wrist pain and disability.

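### The fixed list of measured health-care costs leaves out secondary surgery and admissions, so the cost comparison is incomplete, and biased to the extent that surgery differs between arms

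*Protocol article*

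**What the plan says.** Under Regarding cost-analysis, the list opens with "Resource use of the following cost-categories will be measured" and then names five health-care items: "Within health care: control visits, X-ray, CT-scan, emergency visits, costs of the intervention (i.e. device"). Two further items follow: "Outside health care: productivity loss, travel costs". Nothing in the wording marks these as examples.

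The second aim, at the end of Background, is to find out whether PEMF will "decrease the incidence of non-unions and avascular necrosis of the scaphoid and therefore the number of secondary surgical interventions". Background also says that "surgery is generally performed only if complications in healing occur", and that operative treatment of complicated healing "is often initiated in a late phase, most often months after the fracture occurred".

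In the economic part of Methods/Design, the ICER numerator is the between-arm difference in total treatment cost, taken from a societal perspective. Regarding cost-analysis sets the horizon at inclusion to 12 months. Regarding the analysis puts bootstrap intervals around the mean cost difference and the ICER.

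Visits are scheduled at 6, 9, 12, 24 and 52 weeks and CT at 6, 12, 24 and 52 weeks, with the statement "All patients will receive the same follow up, as described above". Methods/Design also describes care that depends on healing: a new plaster if the fracture has not consolidated, and a removable splint for pain after twelve weeks. Neither is on the cost list.

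**The concern.** Surgery is the direct medical cost most likely to depend on whether the fracture heals, and the article itself makes it an effect to be tested. A total that leaves it out is not the quantity that the ICER is defined on.

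The items that are listed can respond little to outcome. Visits and CT follow one schedule in both arms, and the device cost is set by arm. Only emergency visits, and any unscheduled visits or imaging, can vary with healing. The health-care cost difference would therefore sit close to the device price, whatever PEMF does to non-union. A real saving from avoided operations would go unseen, and so would a real excess of operations.

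**Working it through.** **The plan's own figures (Background).**
- Added device cost: 750 × EUR 1,250 = EUR 937,500. Reproduced.
- Workdays saved: 750 × 46 = 34,500. Reproduced (30% of 155 is 46.5; the plan uses 46).
- Productivity saving: 34,500 × EUR 303.21 × 0.8 = EUR 8,368,596. Reproduced.
- Productivity saving per patient: 8,368,596 / 750 = about EUR 11,158.

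Surgery appears on neither side of this projection.

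**Inputs for the omitted component.**
- Non-union rate: 5-21% (Abstract).
- Relative reduction: 30-71%. Background gives 30% as faster healing with ultrasound, and 71% from electrical stimulation of scaphoid fractures that were already non-unions. Neither is an estimate of prevention by PEMF. They serve only as illustrative ends of a range.
- Share of non-unions operated: 50-100% (assumption; the article gives no rate).
- Cost per operation: EUR 1,000-10,000 (assumption; the article names sources for unit costs but no figure).

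**Formula.** Omitted difference per patient = non-union rate × relative reduction × share operated × cost per operation.

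| Case | Operations avoided per patient | Per 54 patients | Omitted EUR per patient | % of EUR 1,250 | % of EUR 11,158 |
|---|---|---|---|---|---|
| Low: 0.05 × 0.30 × 0.5, EUR 1,000 | 0.0075 | 0.4 | 8 | 0.6 | 0.1 |
| Middle: 0.10 × 0.71 × 1, EUR 5,000 | 0.071 | 3.8 | 355 | 28 | 3 |
| High: 0.21 × 0.71 × 1, EUR 10,000 | 0.1491 | 8.1 | 1,491 | 119 | 13 |

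With the most favourable rates, an operation would have to cost 1,250 / 0.1491 = about EUR 8,384 for avoided surgery to pay for the device.

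**If surgery does not differ between arms.** The expected bias in the mean difference is zero, but the spread is still incomplete. As an illustration, suppose 10% of each arm is operated at EUR 5,000. The omitted cost then has a per-patient standard deviation of √(0.1 × 0.9) × 5,000 = EUR 1,500. With 54 per arm, its contribution to the standard error of the difference is 1,500 × √(2/54) = about EUR 289, which the bootstrap of the recorded costs would not see.

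**The case against.** The strongest reply is that the evaluation is societal and productivity dominates it. On the plan's projection, even the extreme EUR 1,491 is about 13% of the productivity saving. Work lost after an operation is still captured by the PRODISQ, so only the direct medical cost goes missing. This stands, and it limits the weight of the point for the societal ICER. It does not help the health-care component, and it leans on a work saving that the trial has yet to show.

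The upper-end inputs are also generous. Methods/Design does not make surgery the automatic consequence of non-union: after twelve weeks an unconsolidated but painless fracture ends treatment, and a painful one gets a splint. Some late surgery may fall beyond 12 months. The Abstract attaches the 71% to fresh fractures, but Background takes it from established non-unions. This too stands, which is why the range starts near zero.

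Two further inferences are tempting but not supported:
- **That the shared schedule of visits and CT is itself an error.** Equal costs cancel in a difference and do not bias it. Unscheduled use could still be counted, because volumes of use are what is multiplied by unit cost.
- **That the surgical part of the second aim has no data.** Secondary surgery is absent from the article's endpoint lists. But a condensed article does not show the case-report form, and patients are seen to 52 weeks.

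It might also be said that the cost list is a detail left to the fuller protocol. That does not hold: the article states a specific list, and the list conflicts with its own aim and its own definition of the numerator.

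**Conclusion.** The point holds as a defect in a stated rule. Followed as written, the cost totals omit secondary surgery and admissions, and their bootstrap spread is incomplete whenever an operation occurs. The cost difference and ICER are biased only to the extent that surgery differs between arms, in either direction.

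A reader might infer that the cost difference is bound to be wrong, or wrong against PEMF. The documents do not support that: the second aim asks whether surgery falls and does not assert that it will, and with no difference in surgery the expected bias is nil.

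The size cannot be fixed from the documents. Under the assumptions shown, it runs from about EUR 8, which is trivial, to EUR 1,491 per patient, which is more than the device costs. Everything above the non-union range rests on assumed or borrowed inputs. The primary endpoint, the sample size and the clinical comparison are untouched. This is a should-fix for the economic aim.

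**What to change.** Under Regarding cost-analysis, add secondary scaphoid surgery and related admissions to the measured health-care categories, together with the plaster changes and splints that Methods/Design already makes dependent on healing. Record them per patient, with dates, at the existing visits to 52 weeks. Value them with the unit-cost sources the section already names. Report the number of patients with secondary surgery by arm, so that the surgical part of the second aim has a stated measure.

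The cost is a few extra case-report-form items at visits already planned and one added line in the cost analysis.

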### Regarding the analysis

Data will be analyzed according to the intention-to-treat principle. Confidence intervals surrounding the mean differential costs will be calculated by the bootstrap method. This method estimates the sampling distribution of a statistic with replacement from original data [41] In addition, bootstrap analysis will also be used to quantify the uncertainty surrounding the incremental cost-effectiveness ratio (ICER) [42].

Results of this analysis will be presented in cost-effectiveness planes and acceptability curves. A cost-effectiveness plane is a graphical presentation of four situations or quadrants in which additional costs and additional health outcome effects of a new therapy are compared to care as usual. The acceptability curve shows the probability of a new therapy being more cost-effective than the usual treatments for various threshold values, i.e. the maximum amount society is willing to pay.

### Regarding patient outcome analysis

As described above, the primary outcome for the cost-effectiveness analysis will be the number of consolidated fractures. In addition, the outcome for the cost-utility analysis will be QALY, based on the scores of the SF-36. The SF-36 is developed to measure general health related quality of life [43]. The survey consists of 36 items and questions, which present respondents with choices about their perception of health over the last week. The following dimensions are included; physical functioning, role limitations due to physical problems, bodily pain, general health, vitality, social functioning, role limitations due to emotional problems and mental health. The scores from the SF-36 can be converted to utilities and hence to QALY's by using the scoring model as developed by Brazier J et al.[44]

### Ethics and consent

The study protocol conforms to the Helskinki Declaration and to local legislation. The local medical ethics committee [45] reviewed and approved the study protocol. All patients have to provide written informed consent before participation in the study.
